### Assignment of interventions

#### Allocation

The PI will generate a blocked randomization list (2,2 per group) using the online software QuickCalcs (www.graphpad.com). Only the PI will have access to the randomization list after its generation.

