### Participants

Patients with LHN due to stroke will be recruited in the Neurorehabilitation Unit of the IRCCS Istituto delle Scienze Neurologiche di Bologna (coordinating center) and the Villa Bellombra rehabilitation Hospital in Bologna (Italy). Subjects will be recruited accordingly to the following eligibility criteria:

Inclusion criteria:
Diagnosis of ischemic stroke of the right medial cerebral artery or right intracranial hemorrhagic stroke, confirmed by encephalic CT scan or MRI;Diagnosis of LHN with specific screening test (asymmetry score in the Bells test > 3);Inpatient or outpatient rehabilitation setting;Age between 18 and 80 years;Time after stroke between 3 weeks and 12 weeks; andAdequate language comprehension to give informed consent.

Exclusion criteria:
Medical instability at the time of enrollment, defined as the acute onset of an unexplained derangement of one or more vital parameters (temperature, blood pressure, pulse rate, respiratory rate, oxygen saturation, level of responsiveness) outside the normal range (e.g., fever, cardiac arrhythmias, respiratory insufficiency) and/or the onset of any new medical condition requiring unexpected additional diagnostic procedures and treatments (e.g., severe pain, reduction of urinary output);Presence of epileptogenic alterations of the EEG and/or previous epileptic seizures;Presence of intracranial implants of a metallic material;Presence of devices that could be altered by r-TMS, such as pacemakers, ventriculoperitoneal derivations, or baclofen infusion pumps;Absence of bone flap following decompressive craniectomy;Presence of alteration in the consciousness-vigilance rhythm;Cortical blindness and/or visual agnosia;Previous psychiatric disorders and/or history of substance abuse;Pregnancy state;Severe deafness not compensated by hearing devices;Severe reduction of visual acuity not compensated by optic lenses; andPrevious diagnosis of cognitive impairment.

Before enrollment in the study, the principal investigator (PI) will check the eligibility criteria. In particular, after verifying the eligibility criteria, the PI (or a delegate) will provide the potentially eligible person with all the information and details relative to the study in a simple language during an interview that will preferably take place in the presence of a caregiver.

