### Data collection and management

All data will be anonymized, and a specific alpha-numeric code will be attributed to each subject after enrolment. All the assessors will be responsible for transfers the data they have collected on paper CRF into the corresponding electronic CRF in the study database shortly after their collection. The study database is configured so that only the PI will be aware of all patient details, including the randomization group, and this information will not be visible to any of the assessors. Statistical analyses over the complete dataset will be performed at the end of data collection. However, interim analyses approved by the local ethical committee may be performed.

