### Oversight and monitoring

A dedicated member of the investigator team other than the PI will assess the completeness of data collection and be involved in monitoring all the clinical trial’s organizational, ethical, and scientific aspects. The PI will declare the end of the enrolment.

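### Allocation is not concealed from the principal investigator, who generates and alone holds the randomization list and also decides eligibility

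*Protocol article*

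**What the plan says.** Four statements in the protocol article bear on this point.

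- **Generation** (Allocation): "The PI will generate a blocked randomization list (2,2 per group) using the online software QuickCalcs".
- **Custody** (Allocation): "Only the PI will have access to the randomization list after its generation".
- **Entry decision** (Participants): "Before enrollment in the study, the principal investigator (PI) will check the eligibility criteria". The next sentence, on informing the candidate, says that "the PI (or a delegate) will provide the potentially eligible person with all the information and details relative to the study". The option to delegate is attached to this interview, not to the eligibility check.
- **Knowledge of groups during the trial** (Data collection and management): the database is set up so that "only the PI will be aware of all patient details, including the randomization group".

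The Blinding section lists the safeguards: T0 is done before randomization, T1 and T2 are rated by an assessor unaware of the group, and the visual scanning therapists are unaware of the allocation. The article describes no step that keeps the next assignment from the person who admits patients.

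**The concern.** Randomization protects the comparison only if whoever admits a patient cannot foresee the arm. Here one role writes the sequence, is its sole holder and judges eligibility. That person could, knowingly or not, admit, defer or decline a candidate in the light of the arm that comes next.

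There is room for such steering. Some entry criteria are matters of judgement, such as adequate language comprehension and medical instability. The window of 3 to 12 weeks after stroke leaves freedom over timing, and inpatients and outpatients both qualify. A further exclusion point follows the pre-test EEG (Safety assessment).

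The stake is a treatment estimate that mixes the effect of stimulation with a difference in who was admitted to each arm. Masked outcome assessment cannot undo that.

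**Working it through.** The plan gives no figure for this point, so there is none to reproduce. The main check sets the sections side by side. A small enumeration then sizes the secondary issue of block predictability.

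**Step 1. Does the enroller know the next assignment?**

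| Function | Who | Section |
|---|---|---|
| Generates the list | PI | Allocation |
| Has access to the list | PI only | Allocation |
| Checks eligibility before enrolment | PI, no delegate named | Participants |
| Informs the candidate | PI or a delegate | Participants |
| Sees the group in the database | PI only | Data collection and management |

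The first three rows settle the matter: the list exists before eligibility is decided, and the person deciding it holds the list. The list holder knows 100% of upcoming assignments at any block size.

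**Step 2. Do the stated safeguards reach the entry decision?**

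- T0 before randomization keeps the baseline score free of knowledge of the arm if the T0 rater lacks the list. It does not hide the list from the PI.
- Masked T1 and T2 assessors protect outcome measurement.
- Masked therapists protect the co-treatment.

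None of the three governs who enters or when.

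**Step 3. Secondary: how predictable is a block of 4?**

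Assumptions: 2,2 per group means fixed blocks of 4 (the text does not say fixed), and the guesser knows every earlier assignment in order. There are 6 orderings of two A and two B, so 6 × 4 = 24 positions.

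- *Determined with certainty* (one arm already used up): AABB and BBAA give 2 positions each, the other four orderings give 1 each. Total 2×2 + 4×1 = 8, and 8/24 = 33.3%.
- *Guessed correctly* (choose the arm with more places left, score 0.5 when tied): AABB and BBAA score 0.5 + 0 + 1 + 1 = 2.5 each; the other four score 0.5 + 1 + 0.5 + 1 = 3 each. Total 2×2.5 + 4×3 = 17, and 17/24 = 70.8%, against 50% by chance.

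For the planned 56 patients (56/4 = 14 blocks), that is 56 × 8/24 = 18.7 determined and 56 × 17/24 = 39.7 guessed correctly, against 28 by chance.

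| Fixed block size | Determined | Guessed correctly |
|---|---|---|
| 4 | 33.3% | 70.8% |
| 6 | 25.0% | 68.3% |
| 8 | 20.0% | 66.6% |

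While the PI holds the list, these figures add nothing for the PI. They matter once custody moves, because the PI would still see past groups in the database.

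**The case against.** **Concealment fails toward one role only.** The list is withheld from everyone else, and assessors and therapists are kept unaware. This stands, and the point is limited to the PI. A reader might infer that allocation is open to the whole team; the text does not support that.

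**Steering is constrained.** Several criteria are objective: imaging-confirmed stroke, a Bells test asymmetry score above 3, age and time since stroke. Baseline BIT is the ANCOVA covariate, so selection on neglect severity would be partly adjusted for. This also stands in part. Adjustment does not reach prognosis that baseline BIT fails to capture, or the timing of entry.

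**The block figures are upper bounds.** The article names no recruiter other than the PI who would know past allocations. The stimulation operator must know the coil position but is given no enrolling role. With two centres and no statement of one list or two, staff who see only their own patients might predict less well. This stands.

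**A full protocol may hold the missing detail.** An article can leave out the mechanics of concealment. Here, however, it positively assigns generation, sole custody and the eligibility check to one role. A fuller document could remove the conflict only by contradicting that.

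**Interim looks and closure of enrolment.** Because the article also says "However, interim analyses approved by the local ethical committee may be performed" and "The PI will declare the end of the enrolment", a reader might infer that the PI could stop recruitment in the light of results. The documents do not support this. The sample size is set at 56, nothing ties closure to interim results, and the handling of interim looks is commonly left to the full protocol or analysis plan. It is a separate topic and forms no part of this point.

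**Conclusion.** The concern holds for the PI. By the article's own rules, the person who decides entry has generated the list and is the only one who can consult it, and no stated safeguard covers that decision. Selection bias is possible; it is not shown.

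The documents do not allow the bias to be sized. A reader might want to express it as a share of the planned effect, but that needs the proportion of patients steered and their difference in prognosis, and the article gives neither.

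The firm quantity is that the list holder knows every upcoming assignment. The 33% and 71% are a secondary upper bound, resting on fixed blocks of 4 and full knowledge of past allocations. The main conclusion needs neither assumption; it needs only that the Allocation and Participants sections mean what they say.

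**What to change.** For patients not yet randomized:

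1. Have a new list generated and held by an existing team member with no role in screening, consent, assessment or treatment. The non-PI member named under Oversight and monitoring is a candidate; if used, that person should be kept out of outcome review, since holding the list unblinds them.
2. Use varying block sizes that are not disclosed to recruiters. Moving custody alone is not enough, because the PI can see past groups in the database.
3. Release each assignment to the stimulation operator only after eligibility, consent and T0 are irrevocably recorded.
4. Remove the PI's view of upcoming assignments.
5. Report how the patients already randomized were allocated, and compare screened with enrolled patients and baseline BIT by arm.

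Trial status gives 10 patients randomized, which left 56 − 10 = 46 to protect at that date. If there was one list of fixed blocks of 4, then 10/4 = 2.5 blocks, so the new list starts mid-block. The half block can leave the arms at most 2 patients apart, which is tolerable and should simply be reported.

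The cost is a short amendment, a new list and one extra step before the first session. No extra patients are needed. The existing team member takes on a small added task.

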#### Blinding

To ensure a double-blind assessment, pre-treatment assessments (T0) will be performed before randomization, whereas post-test (T1) and follow-up (T2) assessments will be carried out by an assessor who will not be aware of the randomization group. The visual scanning protocol will be administered by therapists unaware of the patient’s allocation to intervention or control arms. Patients themselves will be instructed not to reveal any information to the assessors on the brain stimulation treatment received.

To minimize biases deriving from inter-rater measurement errors, the following interventions will be performed before the start of the trial:
Collegial assessments of patients who are not candidates for enrolment by the various assessors involved in the trial to standardize the administration modalities and resolve any discrepancies between scoring procedures.The subsequent development of an “assessment manual” containing all information for administering and scoring procedures.

### Data collection and management

All data will be anonymized, and a specific alpha-numeric code will be attributed to each subject after enrolment. All the assessors will be responsible for transfers the data they have collected on paper CRF into the corresponding electronic CRF in the study database shortly after their collection. The study database is configured so that only the PI will be aware of all patient details, including the randomization group, and this information will not be visible to any of the assessors. Statistical analyses over the complete dataset will be performed at the end of data collection. However, interim analyses approved by the local ethical committee may be performed.

### Statistical analysis

Changes in all endpoints will be assessed across groups (r-TMS plus VS and SHAM plus VS) and across time (at post-test and 12 weeks follow-up assessment). BIT, TAP, CBS, and the motor function tests (MI, TCT, and FIM^tm^) provide standard scores, separated for each test, and scores including a general performance with cutoffs that allow discriminating pathological performance. vABI and IHTT are continuous variables based on neurophysiological data. Differences in primary and secondary outcomes for each indicator will be analyzed between the pre-test baseline (T0), post-test(T1), and follow-up (T2) phases for both groups of patients (group r -TMS plus VS and SHAM plus VS group).

The pretest-posttest follow-up control group design is often analyzed with the posttest and follow-up as dependent variables and the pretest as covariate (ANCOVA) [34, 35] or with the difference between posttest and pretest as dependent variable (CHANGE) [36, 37]. The choice of one of these two methods should consider two assumptions: homogeneity vs. heterogeneity of the study population (i.e., group differences at pretest) and normal data distribution.

In general, ANCOVA is preferable in randomized controlled trials as treatment assignment is based on randomization [34–36], and this may prevent data heterogeneity. However, in heterogeneous data, a measure of gain is preferable (i.e., CHANGE). Both methods have more power if data are normally distributed [36].

In our study, we will verify first the two assumptions mentioned above for each outcome measure and, afterward, we will adopt the appropriate approach:
Homogeneity vs. heterogeneity: For each outcome measure, the ANCOVA assumption of homogeneity of regression slopes will be verified [38]. In case the assumption is violated, a CHANGE measure (i.e., a score of gain in the specific outcome) will be considered in a 2 × 2 mixed-model ANOVA with the between factor group and the within factor time (posttest and follow-up).Normal distribution: Our primary outcome (the Behavioral Inattention Test) data will be analyzed after linear logistic transformation accordingly to the Rasch calibration, which ensures normal data distribution [39]. For the secondary outcomes, in the case normal distribution is not verified, a linear logistic transformation will be performed.In the case assumptions are verified, a mixed-model ANCOVA will be used with a 2 × 3 design, where the “between” factor will be the randomization group and the “within” factor will be the time of assessment, with the covariate pre-test baseline (T0) used to control for the LHN level before the beginning of the rehabilitation protocols.

In all cases, a two-tailed *t* test for independent samples will be employed to investigate the differences between groups. Data analysis will be performed using the MatLab (The Mathworks Inc.) and SPSS (version 13) softwares. We will accept a significance level of 5% (i.e., *p* value = .05) corrected for multiple comparisons when needed. Data from all randomized patients will be included in the analyses. Should data be missing at follow-up, data will be analyzed according to the intention to treat principle. However, participants will be contacted by telephone in the proximity of follow-up to ensure participant retention.

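### The switch from ANCOVA to change scores is triggered by a slope test that does not match its stated reason, and change scores do not remedy unequal slopes

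*Protocol article*

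**What the plan says.** All statements are in the Statistical analysis section of the protocol article.

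- The general preference is clear: "In general, ANCOVA is preferable in randomized controlled trials as treatment assignment is based on randomization".
- The choice between ANCOVA and change scores is said to turn on two conditions: "homogeneity vs. heterogeneity of the study population (i.e., group differences at pretest) and normal data distribution". Heterogeneity is thus glossed as a baseline difference between the arms, and the consequence drawn is "However, in heterogeneous data, a measure of gain is preferable (i.e., CHANGE").
- The choice follows a check on the data: "we will verify first the two assumptions mentioned above for each outcome measure and, afterward, we will adopt the appropriate approach".
- The check actually specified, under the label of homogeneity versus heterogeneity, is a different one: "For each outcome measure, the ANCOVA assumption of homogeneity of regression slopes will be verified".
- If it fails: "In case the assumption is violated, a CHANGE measure (i.e., a score of gain in the specific outcome) will be considered". The gains then go into an ANOVA of group by time (posttest and follow-up), with no baseline covariate named.
- If it passes: "In the case assumptions are verified, a mixed-model ANCOVA will be used with a 2 × 3 design", with T0 as covariate.

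The rule covers the primary BIT and every secondary outcome. No level is given for the slope test.

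**The concern.** Two things do not fit together. First, the trigger does not examine the stated reason for switching. Slopes can differ when the pretest means are identical, and pretest means can differ when the slopes are equal. In a randomised trial a pretest difference arises by chance, and that is the situation in which baseline adjustment is most useful.

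Second, the fallback does not treat the condition that triggers it. If the relation of outcome to baseline differs between arms, subtracting the baseline leaves that difference in place.

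At stake is which estimate of the BIT effect is reported. When the slope test is significant, the analysis moves from the method that the article itself prefers to one that is usually less precise and that carries part of any chance baseline imbalance into the treatment estimate. In a trial of 28 per group such imbalance is not negligible.

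**Working it through.** **Inputs from the article (Sample size section).** 28 per group with 10% loss leaves 28 × 0.90 = 25.2, so 25 per arm is used. The printed formula gives 2 × 10.5 × 3.1² / 2.84² = 25.02, close to the stated 25.2, if 3.1 is read as an SD and 2.84 as a difference. Read as labelled (variance and squared difference) it gives 2 × 10.5 × 3.1 / 2.84 = 22.92, which does not reproduce. The planned effect is then 2.84 / 3.1 = 0.92 SD. The labelled reading would give √(2.84 / 3.1) = 0.96 SD, so little turns on this.

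**Inputs assumed.** The baseline–outcome correlation (rho), the slopes in each arm and a 5% level for the slope test are not in the article. Ranges are shown.

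**1. Does the change score remove unequal slopes?** Let Y = a_g + b_g·X + e in arm g. Then Y − X = a_g + (b_g − 1)·X + e. The slope difference is (b_1 − 1) − (b_0 − 1) = b_1 − b_0, unchanged. In simulation with slopes 0.7 and 0.3 it was −0.40 on both scales.

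**2. Precision.** With equal SDs, the variance of the group difference is proportional to 2(1 − rho) for change and 1 − rho² for ANCOVA. The ratio is 2(1 − rho)/(1 − rho²) = 2/(1 + rho).

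| rho (assumed) | 0.3 | 0.5 | 0.7 | 0.9 |
|---|---|---|---|---|
| Variance, change / ANCOVA | 1.54 | 1.33 | 1.18 | 1.05 |

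**3. Sensitivity to baseline imbalance.** Given a baseline difference d, the change estimate is shifted by (average slope − 1)·d; the ANCOVA estimate is shifted by about 0. One standard error of d is √(2/25) = 0.28 SD. At an average slope of 0.6 the shift is 0.4 × 0.283 = 0.113 SD in size, or 0.113/0.92 = 12% of the planned effect. This applies only when the switch fires.

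**4. How often it fires.** With truly equal slopes, about 5% of the time per outcome. In simulation it fired in about 33% of trials with slopes 0.7 and 0.3, and in 69% with slopes 0.9 and 0.3. When it fired and the effect was 0.5 SD, ANCOVA and change scores disagreed on significance in about 12% to 22% of trials.

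**5. Power of the whole rule.** Simulation of one post-baseline time point, normal data, 25 per arm, average slope 0.6, residual SD 0.8; 4,000 trials per row, 6,000 in the last:

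| Slopes | Effect (SD) | ANCOVA throughout | Rule | Loss (points) |
|---|---|---|---|---|
| equal | 0.92 | 97.2% | 96.9% | 0.3 |
| 0.7 / 0.5 | 0.92 | 97.7% | 96.9% | 0.8 |
| 0.75 / 0.45 | 0.92 | 96.8% | 96.0% | 0.8 |
| 0.9 / 0.3 | 0.92 | 95.2% | 92.7% | 2.5 |
| 0.9 / 0.3 | 0.6 | 67.0% | 61.8% | 5.2 |

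A repeat with 20,000 trials per row gave losses of 0.1, 0.4, 0.8, 2.7 and 5.1 points. The loss also depends on the average slope. In a separate set of 20,000 trials at 0.92 SD, a slope gap of 0.4 cost 0.6 points for slopes 0.9/0.5 (98.9% to 98.3%) and 2.3 points for slopes 0.7/0.3 (94.2% to 91.9%).

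**6. Validity.** Type I error under the rule was 4.5% to 5.3% across the runs. The mean estimate equalled the true effect for ANCOVA, for change scores and for the rule.

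**The case against.** The strongest defence is that nothing here invalidates the trial, and that is right. Several stronger readings are tempting and should not be drawn.

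- *That the rule biases the result or inflates type I error.* It does neither over randomisation. The bias in step 3 is conditional on the imbalance that a particular trial happens to have.
- *That change scores need a slope of 1 in both arms, a stricter assumption than the one just rejected.* Under randomisation the difference in mean change is unbiased whatever the slopes are. A slope other than 1 costs efficiency and leaves conditional bias; it does not destroy validity.
- *That the primary analysis is left open.* The article names a default, a trigger and a fallback. This is a conditional rule, weaker than one fixed model but not a free choice. An article may also leave the level of the slope test to a fuller document.
- *That about 5 points of power are lost.* That needs an assumed slope gap of 0.6 and an effect of 0.6 SD. Neither is in the article, whose own effect is about 0.92 SD.
- *That a false switch somewhere is likely.* For eight outcomes the figure would be 1 − 0.95⁸ = 34%, but only if they were independent. Several of them measure neglect, and a switch on a secondary outcome does not alter the BIT result.

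Two further limits stand. The 0.28 SD imbalance is one standard error, and the mean absolute imbalance is smaller, about 0.23 SD. The simulations also use one time point, whereas the plan analyses T1 and T2 together, so the power figures are illustrative.

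The defence does not answer the mismatch between reason and trigger, nor the algebra in step 1. The soft verb used for the fallback does not make this a mere option, because ANCOVA is expressly conditional on passing the check.

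**Conclusion.** The point holds as a defect of method with a small average cost. The switch is justified by one condition and triggered by another, and the fallback leaves the triggering condition untouched. It is less precise whenever rho is below 1 (5% to 54% more variance for assumed rho of 0.9 to 0.3, equal SDs), and it passes chance imbalance into the estimate.

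At the planned effect of about 0.92 SD the overall power loss is under about 1 point for slope gaps of 0.2 to 0.3 and 2 to 3 points for a gap of 0.6. It reaches about 5 points only at an assumed 0.6 SD effect with that large gap. In a single trial in which the switch fires, the consequence can be larger than these averages suggest, since the two methods can then disagree on significance.

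The documents do not support calling the rule invalid. The change is worth making because it removes an avoidable loss at no cost and follows the article's own stated preference for ANCOVA. The sizes rest on the assumed rho, slopes and 5% slope test; the mismatch and the unchanged slope difference rest on no assumed figure.

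**What to change.** In the Statistical analysis section:

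1. State that ANCOVA adjusted for T0 is the analysis for the BIT and for every secondary outcome, whatever any slope test or baseline comparison shows.
2. Delete the switch to the change-score ANOVA and the sentence that ties it to heterogeneous data.
3. Add, as a pre-specified sensitivity analysis, a model with group × (T0 minus overall mean T0), and report the group difference at mean T0. It should be reported regardless of the slope test; adding it only after a significant test would again make the model depend on the data.
4. Show change scores descriptively only.

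The cost is analysis wording. No data collection, sample size or patient procedure changes. The Trial status section reports ten patients randomised, and Data collection and management places the main analysis at the end of data collection. At the stage the article describes, the change can therefore be made before outcome data are examined by group.

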#### Neurophysiological secondary endpoints

Finally, in the present study, lateralized visual processing’s neurophysiological correlates are collected to investigate the common interhemispheric imbalance in LHN [1, 10, 28]. In this study, the EEG will be recorded while patients perform a visual detection task (Fig. 2) seated at a distance of 50 cm from the computer’s screen. Patients will be prompted to fix a central fixation cross on a screen while visual stimuli are presented. Stimuli will be small yellow squares (1 cm × 1 cm) shown in a black background to detect color contrast between the stimuli and the background easily. Each trial will start with a white central fixation cross over a black background. Then, after a varying stimulus onset asynchrony between 640 and 960 ms (steps of 80 ms), a stimulus will be presented randomly on the right or the left of the fixation cross on a view distance angle 28° along the midline. Stimuli will be displayed for 96 ms; before the subsequent trial, a black background with the fixation cross will be presented for 1000 ms (Fig. 2). In general, the visual detection task consists of a passive visual task with lateralized stimuli, and participants will be prompted to keep the fixation during all tasks [7, 8]. Whenever participants lose the fixation, feedback will be provided to recover it. Overall, 256 stimuli will be presented in 4 blocks of 64 stimuli, where the overall task will have an average duration of 20 min. The EEG will be recorded from 18 Ag/AgCl-cup electrodes according to the 10/20 system referenced to the linked ear lobes. The EEG signal will be recorded from electrodes: Fz, Cz, Pz, C4, C3, P4, P3, F4, F3, Oz, O1, O2. Impedance for EEG and electrooculogram (EOG) electrodes will be kept below 10 kΩ. Off-line, the amplitude in microvolt (μv), and the latency in milliseconds (ms) of the negative peak of the N100 VEP component will be analyzed separately for left and right-presented stimuli in correspondence of posterior electrodes [8]. Then, indexes of interhemispheric imbalance will be extracted. In particular, here we propose the Visuospatial Attention Bias Index (vABI), which is based on N100 peak amplitude and interhemispheric transmission time (IHTT) [29, 30], which is a further index of hemispheric imbalance, based on N100 peak latency.

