**Fig. 2 Fig2:**
[figure not shown]
Visual detection task. Each trial starts with a central fixation cross for a jittered time between 640 and 960 milliseconds (ms), then a stimulus is presented randomly either on the left or on the right of the fixation cross for 96 ms. After stimulus presentation, a fixation cross remains for 1000 ms, and then a new trial starts

Note. The vABI will be calculated as a lateralization index [31] for the N100 amplitude. The vABI will be extracted in two steps. First, N100 for left and right presented stimuli will be calculated in the averaged activity from posterior electrodes (i.e., mean of P3 and P4) to have a signal of the two hemispheric activations after lateralized stimulus presentation. Then, for each participant, the difference in the activations for lateralized stimuli will be calculated as the difference between the resulted N100 peaks for left and right-presented stimuli (i.e., vABI = N100 amplitude for right stimuli − N100 amplitude for left stimuli). Such an index can measure interhemispheric imbalance as it reflects the difference in the activation of the two hemispheres in response to lateralized stimuli. Similarly, based on N100 peak latency, we will compute the IHTT [29, 30], an indicator of the EEG signal’s transmission times from one hemisphere to the other. In particular, we will calculate the IHTT as the difference between the latencies of the negative peak of N100 for left presented stimuli on the posterior electrodes P3 and P4 (i.e., IHTT = N100 latency on P4 - N100 latency on P3), thus constituting a single index in milliseconds of the interhemispheric transmission times specifically for left presented stimuli.

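### The logistic fallback for non-normal secondary outcomes cannot be carried out for vABI and IHTT, and Rasch calibration does not ensure normality

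*Protocol article*

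**What the plan says.** All statements are in the protocol article, under Methods.

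- **Scope of the check** (Statistical analysis): "we will verify first the two assumptions mentioned above for each outcome measure". The two assumptions are homogeneity and normal distribution, so every secondary endpoint is checked for normality.
- **Primary outcome** (Statistical analysis): the BIT is analysed after a "linear logistic transformation accordingly to the Rasch calibration, which ensures normal data distribution". This step is unconditional.
- **Secondary outcomes** (Statistical analysis): "For the secondary outcomes, in the case normal distribution is not verified, a linear logistic transformation will be performed". The article names no exemption, rescaling or other remedy for non-normality.
- **Nature of the two indexes** (Statistical analysis): "vABI and IHTT are continuous variables based on neurophysiological data". Neurophysiological secondary endpoints lists them among the secondary endpoints.
- **Definitions** (note under Fig. 2): "vABI = N100 amplitude for right stimuli − N100 amplitude for left stimuli" and "IHTT = N100 latency on P4 - N100 latency on P3". The amplitudes are in microvolts and the latencies in milliseconds.

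**The concern.** There are two separate errors.

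First, the fallback is written for all secondary outcomes, but a logistic transformation suits only a quantity that can be expressed as a share between two fixed limits. Each neurophysiological index is one measurement minus another. It can fall on either side of zero and has no upper limit. If the normality check fails for one of them, the prescribed step gives no usable number. The analyst must then improvise after seeing the data, which is what a stated rule is meant to prevent.

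Second, the article treats normality of the BIT as secured by Rasch calibration. Calibration concerns the measurement scale. It does not decide how patients are spread along that scale. Moreover, the covariance model needs approximately normal residuals, not normal scores. A reader who accepts the sentence may see no reason to inspect the residuals of the primary model.

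**Working it through.** The plan gives no figure to reproduce here. The check has three parts.

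**1. Does the transformation exist for vABI and IHTT?**

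The article does not define the term. It is read as the log-odds, ln(x/(1 - x)), because the sentence before the fallback ties the same term to Rasch calibration, whose measures are in log-odds. The formula needs 0 < x < 1. The values below are illustrative, because the article gives no observed ones.

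| x (microvolts or ms) | x/(1 - x) | ln(x/(1 - x)) |
|---|---|---|
| -20 | -20/21 = -0.95 | undefined |
| -5 | -5/6 = -0.83 | undefined |
| 0 | 0 | minus infinity |
| 2 | 2/(-1) = -2 | undefined |
| 15 | 15/(-14) = -1.07 | undefined |

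Only differences strictly between 0 and 1 unit have a result, and that depends on the unit: 0.5 ms gives ln(0.5/0.5) = 0, but the same interval written as 500 microseconds is undefined. The Discussion expects active stimulation to make vABI smaller, so values near zero are plausible.

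**2. Would another reading rescue the rule?**

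- *Inverse function, 1/(1 + exp(-x)).* This can be computed. However, 5 ms becomes 1/(1 + 0.0067) = 0.993 and 15 ms becomes 0.9999997, so a 10 ms difference between patients shrinks to about 0.007. The result depends on the unit, is not linear and is not made normal.
- *Rescaling to 0-1 first.* The indexes have no natural limits. If the observed minimum and maximum are used, those two patients become exactly 0 and 1, and their log-odds are minus and plus infinity.

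**3. Does Rasch calibration ensure normality?**

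Data were simulated to fit the Rasch model exactly. The assumptions are 40 yes/no items with difficulties evenly spaced from -2.5 to 2.5, maximum-likelihood person measures, and minimum and maximum scores moved inward by 0.3. There were 2,000 samples of 56, the planned total in Sample size. The Shapiro-Wilk test was applied at 5%. Skewness and kurtosis come from one sample of 20,000 per scenario.

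| Assumed patient distribution (logits) | Skewness | Excess kurtosis | Normality rejected |
|---|---|---|---|
| Normal, mean 0.5, SD 1 | 0.10 | 0.36 | 11% |
| Skewed, 3 minus an exponential with mean 1.3 | -1.40 | 3.78 | 86% |
| Two clusters at -1.8 and 2, SD 0.5 each | 0.04 | -1.46 | 100% |

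The calibrated measures keep the shape of the patient population, even with perfect model fit.

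**The case against.** **The fallback is conditional.** It applies only after a failed normality check, and nothing in the article says that vABI or IHTT will fail. This stands. If they pass, they are analysed in original units and the problem never arises. But a contingency rule has to work when it is triggered, and this one does not.

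**The term is undefined, and detail may sit in the full protocol or analysis plan.** The first half stands, which is why the other readings were worked through; none gives a suitable rule. The second half does not answer the point. The article states the transformation and applies it to all secondary outcomes, so the fault lies in what is written.

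**Stronger readings.** A reader might infer three further things that the document does not support.

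- *That scores at the end of a scale become infinite, and that this is a defect in itself.* It is true of the bare formula, but a routine scoring rule for extreme scores removes it, and an article may leave such a rule to the full document. The article gives no limits for the CBS, MI, TCT or FIM and does not say that end scores are expected.
- *That a logistic transformation is useless for bounded scores.* It can reduce skewness in such scores. The objection to it there is only that the scale of analysis is chosen by a test on the trial's own data.
- *That the primary analysis is damaged.* The BIT transformation is fixed in advance. No bias, loss of power or change in type I error has been shown. Normal scores are not what the model requires, so the false sentence does not by itself invalidate the comparison.

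**Conclusion.** The point holds in two limited parts.

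1. The stated fallback cannot be carried out for two secondary endpoints, vABI and IHTT, when it is triggered. Under the log-odds reading, every zero, negative or above-1 value lacks a finite result. This follows from the article's own definitions. It rests on that reading of an undefined term, but the obvious alternatives are also unsuitable. How likely the trigger is cannot be judged from the article.
2. The claim that Rasch calibration makes the data normal is false. The 86% and 100% rejection rates belong to assumed item sets and patient distributions, not to the BIT. They disprove the general claim and do not predict what this trial will find.

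The consequence is a gap in the rule for two secondary endpoints and a wrong assurance for the primary one. The sample size and the choice of the BIT measure are not affected.

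**What to change.** - **vABI and IHTT:** remove the logistic fallback. Analyse both in microvolts and milliseconds as the group difference adjusted for the T0 value.
- **Other secondary outcomes:** state the analysis scale of each one now, instead of letting a normality test decide it.
- **Sensitivity analysis:** for the same adjusted difference, report a confidence interval and p value from a bootstrap or a re-randomization test that respects the blocked allocation. Do this in all cases, not only when residuals look poor, so that one data-dependent switch does not replace another.
- **BIT:** keep the Rasch-based measure, delete the clause that it ensures normality, and state that model residuals will be checked.

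The cost is a change of analysis wording and a little extra computation. No visit, measurement or patient number changes. The article reports ten patients randomized and recruitment still open, so the change should be recorded and dated before outcomes are compared between groups.
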